6.2. INFORMATION AND CONSENT (OR WAIVER OF CONSENT)

Those who meet the eligibility criteria will be provided with a Patient Information Sheet during one of their routine consultations with their treating surgeon. The participant will have the opportunity to discuss any questions with their surgeon before giving their consent. Those who are agreeable to participate will be asked to complete a hardcopy consent form prior to data being entered into the database. Participants would have time from their initial consult to the time of surgery which is generally 1 week to provide consent. The time to give consent will not be less than 24 hours.

**7. OUTCOMES**

7.1. DEFINITION OF OUTCOMES

Outcome measures that are being assessed relate to the efficacy of Savi Scout® in localising non-palpable breast lesions and axillary lymph nodes.

**8. STATISTICAL CONSIDERATIONS**

8.1. SAMPLE SIZE OR POWER CALCULATION

Power Calculation - with n=1000 patients per group, the upper limit of the observed one-sided 95% confidence interval for the difference between failure rates (seed vs wire) is expected to be less than 0.9% with 80% power, assuming the two methods both have an expected failure rate of 0.6%. Hence, if a 0.9% difference is considered an acceptable equivalence margin (eg. 0.6% for wire and 1.5% for seed), 1000 patients per group should be sufficient to establish equivalence.

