**Ethics Statement:**

The study will be conducted in accordance with the *National Statement on Ethical Conduct in Human Research* (2007) ([Link to National Statement](https://www.nhmrc.gov.au/about-us/publications/national-statement-ethical-conduct-human-research-2007-updated-2018)) , the *CPMP/ICH Note for Guidance on Good Clinical Practice* ([Link to CPMP/ICH](https://www.tga.gov.au/publication/note-guidance-good-clinical-practice-july-2000) ) and consistent with the principles that have their origin in the Declaration of Helsinki. Compliance with these standards provides assurance that the rights, safety and well-being of trial participants are respected.

| **Protocol Title** | An Audit of Savi Scout ® Radar localization for non-palpable breast lesions |
| --- | --- |
| **Objectives** | The primary objectives of iBRA-net Study are:   - To evaluate the efficacy of localization of non-palpable breast lesions with Savi Scout ®. - To establish the efficacy of axillary node marking with Savi Scout ®.   The secondary objectives are:   - To compare the efficacy of Savi Scout ® with hookwire locations of non-palpable breast lesions. |
| **Study design** | Prospective Audit |
| **Planned sample size** | 1000 (worldwide), 50 (COBL) |
| **Selection criteria** | All patients over the age of 18 electing to undergo a breast conserving localization procedure or axillary nodal marking using the Savi Scout ® System will be eligible for inclusion. |
| **Study Procedure** | Potential participants will be identified prospectively by consultant surgeons. Simple demographic, procedure and process data will be contemporaneously collected for each participant. Data will be recorded in an anonymized format using a unique alphanumeric study identification number on a secure web-based database (REDCap) designed by Vanderbilt University and hosted by Manchester University NHS Foundation Trust/Manchester University. |

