4.2. EXPECTED PARTICIPANT NUMBERS

1000 globally, 50 from Chris O’Brien Lifehouse

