**5. STUDY PARTICIPANTS**

5.1. INCLUSION CRITERIA

Patients undergoing a breast conserving localization procedure or axillary nodal marking using the Savi Scout ® System.

18 years of age

Willing to participate in the study.

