**6. STUDY PROCEDURES**

6.1. INVESTIGATION PLAN

The multicentre component of the trial involves a prospective audit of information relating to the use of Savi Scout®.

This involves documenting this data into a secure web-based Redcap database.

The dataset collected is the same from every international site.

There is no intervention that is carried out for the study as this is an audit.

The procedures related to Savi Scout® placement are part of normal practice and are not influenced by this study given the collection of data occurs after the decision to use Savi Scout®. Savi Scout® is an established technology for localisation of impalpable breast lesions and axillary nodes at Chris O’Brien Lifehouse.

This audit will have data contributed from multiple sites globally. The information collected will investigate the margin status of excision, accuracy of placement, timing of the placement of Savi Scout®, and the proportion of Savi Scout® placed at the time of biopsy, pathological weight of specimen, size of MRI bloom around Savi Scout® , transcutaneous detection rate, reoperation rate, complications, cancellation rate on day of surgery, reason for cancellation on day of surgery, time of day of start of surgery and identification rate of axillary nodes using Savi Scout.

Comparative analysis will be performed with the same parameters for participants that have undergone hookwire-localisation of impalpable breast lesions. Information of the hookwire-localisation cohort have been recruited from Manchester University NHS Foundation Trust/Manchester University.

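### The power statement assumes 1000 patients per group, but the planned 1000 mix breast and axillary Savi Scout patients and the wire cohort size is not given, so 80% power is not assured

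*Protocol*

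**What the plan says.** - **Power.** Section 8.1 and the synopsis row on statistical considerations compare failure rates between seed and wire "with n=1000 patients per group". The criterion is that "the upper limit of the observed one-sided 95% confidence interval" for the difference "is expected to be less than 0.9% with 80% power", with an assumed failure rate of 0.6% for both methods.
- **Enrolment.** Section 4.2 expects "1000 globally", of which 50 come from the local site. The synopsis gives the same figures.
- **Who counts towards the 1000.** Section 5.1 admits "Patients undergoing a breast conserving localization procedure or axillary nodal marking using the Savi Scout" system. There is no split between the two uses and no minimum number of breast-lesion patients. Axillary marking is one of the two primary objectives in section 3.1.
- **What is compared with wire.** Section 3.2 makes the comparison with hookwire a secondary objective and confines it to non-palpable breast lesions. Section 6.1 does the same.
- **Where the wire patients come from.** Section 6.1 says: "Information of the hookwire-localisation cohort have been recruited from Manchester University NHS Foundation Trust/Manchester University". The protocol nowhere gives the size of that cohort.

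**The concern.** The calculation needs two groups of 1000 patients who can be compared on breast-lesion localisation. The protocol secures neither group.

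On the Savi Scout side, the 1000 include patients marked only in the axilla. They have no wire counterpart and add nothing to the comparison. Section 8.1 speaks only of patients; the restriction to breast lesions follows from sections 3.2 and 6.1. On the wire side, no number supports the other 1000.

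This is the only sample-size justification in the protocol. If the comparison is later reported as showing equivalence, readers will rely on a power figure that may not describe the groups analysed.

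**Working it through.** **Inputs from section 8.1.** Failure rate p = 0.006 in both groups (true difference 0), margin 0.009, one-sided 5% (z = 1.645), power 80% (z = 0.842). No allowance for non-evaluable patients is stated, so none is used.

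**Formula.** Unpooled (Wald) normal approximation, with p(1 − p) = 0.006 × 0.994 = 0.005964:

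SE = √[0.005964 × (1/n₁ + 1/n₂)], power = Φ(0.009/SE − 1.645).

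**Reproducing the protocol's figure.** At 1000 per group, SE = √(0.005964 × 0.002) = 0.003454. The margin that gives exactly 80% power is (1.645 + 0.842) × 0.003454 = 0.859%, which rounds to the stated 0.9%. With the margin at exactly 0.9%, power is Φ(2.606 − 1.645) = Φ(0.961) = 83.2%, and 911 per group would be enough. The calculation is sound for the groups it assumes and leaves a little room.

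**Power for other group sizes.** The axillary-only shares and wire sizes below are assumptions, because the protocol gives neither.

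| Savi Scout breast patients | Wire patients | Power |
|---|---|---|
| 1000 | 1000 | 83.2% |
| 900 (10% axillary-only) | 1000 | 81.4% |
| 800 (20%) | 1000 | 79.2% |
| 700 (30%) | 1000 | 76.4% |
| 600 (40%) | 1000 | 73.0% |
| 1000 | 500 | 68.5% |
| 1000 | 300 | 55.0% |
| 800 (20%) | 300 | 53.1% |
| 1000 | 2000 | 91.4% |
| 600 (40%) | 2000 | 80.5% |

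**Break-even for 80%.** The condition is 1/n₁ + 1/n₂ ≤ (0.009/2.486)²/0.005964 ≈ 0.002197. With 1000 in one group, the other needs 1/(0.002197 − 0.001), which is 836 patients. So with 1000 wire patients, an axillary-only share of up to about 16% can be absorbed. With 800, 700 or 600 Savi Scout breast patients, the wire cohort must reach 1057, 1302 or 1887.

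**Sensitivity to the interval method.** Section 8.1 does not name the method. At the full 1000 per group and a 0.9% margin, a Newcombe limit gives 77.6% power and a Farrington-Manning test 74.7%. The room for axillary-only patients exists under the Wald limit but not under these two.

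**The case against.** The strongest reply is that the two statements can be reconciled. Only Savi Scout users are eligible, so the 1000 is naturally the Savi Scout group, and the wire cohort is additional. If that cohort has about 1000 patients and few Savi Scout patients are axillary-only, the calculation stands. Much of this is right, and it rules out three stronger readings:

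- **That 80% power will not be reached.** A reader might infer this, but an unstated wire cohort is not necessarily a small one. A cohort of 2000 would give 91.4%, and moderate axillary-only shares cost little: 10% and 20% give 81.4% and 79.2% with 1000 wire patients.
- **That the 1000 must be divided between the two methods.** The eligibility criteria do not support a 500 and 500 split.
- **That recruitment will stop at 1000 with the breast comparison short.** The protocol gives an expected number and calendar dates for recruitment, and no such stopping rule.

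Also, a patient with both a breast and an axillary reflector still counts for the comparison; only axillary-only patients reduce it.

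The reply does not remove the mismatch. Even on the kindest reading, the Savi Scout comparison group equals 1000 only if no patient is axillary-only, although axillary marking is a primary objective and such patients are eligible. The wire number is still needed to support the other half of the calculation.

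**Conclusion.** The concern holds in a limited form: the stated 80% power is not assured, and cannot be verified from the protocol, for the groups that will be compared. Over the compositions tabulated, power runs from about 53% to 91%. That range rests on assumed axillary shares and wire cohort sizes, the protocol's 0.6% failure rate in both groups, the 0.9% margin, a one-sided 5% level and the Wald approximation. The protocol's arithmetic is not at fault; the stated group size does not match the population enrolled for that comparison.

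The point is of moderate weight. The wire comparison is a secondary objective, and the primary objectives evaluate Savi Scout itself without needing the wire cohort. It still merits correction, because this comparison is the only stated basis for the sample size.

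**What to change.** In the synopsis, section 4.2 and section 8.1:

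1. State how many Savi Scout breast-lesion patients are expected to enter the wire comparison.
2. Report axillary-only patients separately and leave them out of that comparison.
3. Insert the actual size of the wire cohort. Section 6.1 describes it as already recruited, so the number should be obtainable.
4. Restate power for those two numbers. If it is below 80%, say so and present the comparison as an estimate with its confidence interval.

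The cost is protocol wording and one recalculation. The stated power may fall. No extra enrolment is required.

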| **Statistical considerations** | Power Calculation - with n=1000 patients per group, the upper limit of the observed one-sided 95% confidence interval for the difference between failure rates (seed vs wire) is expected to be less than 0.9% with 80% power, assuming the two methods both have an expected failure rate of 0.6%. Hence, if a 0.9% difference is considered an acceptable equivalence margin (eg. 0.6% for wire and 1.5% for seed), 1000 patients per group should be sufficient to establish equivalence. Simple summary statistics will be calculated for each outcome and regression analysis used to control for predictive variables. Data will be tested for distribution and differences between groups using unpaired t-tests, Mann-Whitney U tests and Chi squared tests as appropriate, based on recruitment. |
| **Time Period of Data Collection** | May 2023 – May 2024 |
| **Duration of the Study** | 1 year |

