3.2. SECONDARY OBJECTIVES

To compare the efficacy of Savi Scout ® with hookwire locations of non-palpable breast lesions.

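### Section 8.1 and the synopsis claim equivalence, but the calculation supports only a one-sided statement: Savi Scout failures less than 0.9 points above wire, which allows up to 2.5 times the assumed wire rate

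*Protocol*

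**What the plan says.** Section 8.1 of the protocol, repeated in the synopsis under statistical considerations, starts from a fixed size, "with n=1000 patients per group", and a single bound. The bound is "the upper limit of the observed one-sided 95% confidence interval for the difference between failure rates (seed vs wire"), which "is expected to be less than 0.9% with 80% power", "assuming the two methods both have an expected failure rate of 0.6"%. It then introduces the margin conditionally: "if a 0.9% difference is considered an acceptable equivalence margin (eg. 0.6% for wire and 1.5% for seed"). From this it concludes that "1000 patients per group should be sufficient to establish equivalence".

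The comparison with wire is the secondary objective in section 3.2: "To compare the efficacy of Savi Scout ® with hookwire locations of non-palpable breast lesions". Section 6.1 describes the comparator as already collected: "Information of the hookwire-localisation cohort have been recruited from Manchester University NHS Foundation Trust/Manchester University". The number of patients in that wire cohort is not given. The planned 1000 in section 4.2 is the total for the audit itself, whose participants all have Savi Scout.

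**The concern.** Equivalence means that the difference lies within the margin in both directions. Section 8.1 examines one direction only, so its conclusion does not follow from its calculation.

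The word also suggests that the two failure rates are alike. The 0.9-point margin is 1.5 times the assumed wire rate, so a pass leaves room for a Savi Scout rate up to 2.5 times that of wire. A reader told that equivalence was established would probably not take it that way. At stake is the strength of the claim that 1000 patients per group can support, not the sample size.

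**Working it through.** **Inputs, all from section 8.1:** 1000 per group; one-sided 95% upper limit for seed minus wire; both true rates 0.6%; margin 0.9 percentage points; 80% power.

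**1. Reproducing the plan's figure (normal approximation, unpooled).**
- SE = sqrt(2 × 0.006 × 0.994 / 1000) = 0.345 points.
- Smallest margin met with 80% power: (1.645 + 0.842) × 0.345 = 0.859 points, which is below 0.9 as stated.
- Taking 0.9 exactly: n = 2 × 0.006 × 0.994 × (1.645 + 0.842)² / 0.009² = 911 per group. Power at 1000 = Φ(0.9/0.345 − 1.645) = 83.2%.
- Full enumeration of the two binomials: 83.5% with the Wald limit, 77.6% with the Newcombe limit.

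So 1000 per group is adequate for the one-sided statement.

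**2. Power for equivalence as the word is normally used.** Both one-sided 95% limits must lie within ±0.9 points, with both rates 0.6%.
- Normal approximation: 2 × 0.832 − 1 = 66.3%. For 80% power, n = 2 × 0.006 × 0.994 × (1.645 + 1.282)² / 0.009² = 1262 per group.
- Enumeration: 67.0% (Wald), 55.2% (Newcombe).

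**3. What the margin allows in relative terms.** (0.6 + 0.9)/0.6 = 2.5. The ratio depends on the wire rate: (0.3 + 0.9)/0.3 = 4.0, and (1.0 + 0.9)/1.0 = 1.9.

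**4. Probability that the upper limit falls below 0.9 points.** Enumeration with 1000 per group. The wire rates of 0.3% and 1.0% are assumptions, shown as a range on either side of the plan's 0.6%.

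| Wire | Savi Scout | Ratio | Newcombe | Wald |
|---|---|---|---|---|
| 0.6% | 0.9% | 1.5 | 41.8% | 49.3% |
| 0.6% | 1.2% | 2.0 | 16.2% | 20.5% |
| 0.6% | 1.5% | 2.5 (at the margin) | 4.8% | 6.5% |
| 0.3% | 0.45% | 1.5 | 76.3% | 84.4% |
| 1.0% | 1.5% | 1.5 | 19.1% | 21.8% |

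By normal approximation the first row is Φ((0.9 − 0.3)/0.386 − 1.645) = 46.4%, where 0.386 points is sqrt(0.006 × 0.994/1000 + 0.009 × 0.991/1000).

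**5. Could a tighter claim be supported at this size?** At a 0.6% wire rate, excluding a doubling means a 0.6-point margin and excluding a 1.5-fold rate means a 0.3-point margin. With both true rates 0.6% and 1000 per group, power is 49-56% and 20-24% respectively. By the formula in step 1, 80% power would need 2049 and 8194 per group.

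**The case against.** Three arguments on the other side have force.

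First, a device at 0.9% against 0.6% differs by 0.3 points, a third of the margin. Any non-inferiority design passes a sizeable share of devices inside its margin. A reader might take the 42-49% for a false-positive rate. It is not one: at the margin itself the pass probability is 4.8-6.5%, close to the nominal 5%. The figure describes how lenient the margin is and nothing more.

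Second, the tolerance is not hidden. The protocol prints 0.6% against 1.5% and makes the margin conditional on being acceptable. With rare events any affordable absolute margin looks large as a ratio. A reader might infer that the margin is clinically wrong, or that it was worked backwards from 1000, since 0.859 rounds to 0.9. The documents support neither. They do not say what excess of failures matters, and the order of the argument does not prove how the margin was chosen. The lack of a stated reason for 0.9 is only missing detail.

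Third, the comparison is secondary. Equivalence appears in neither the hypothesis (section 2) nor the endpoints (section 4.4). That limits the weight of the point but does not remove it, because section 8.1 is the only sample-size basis in the protocol and it draws the equivalence conclusion explicitly.

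**Conclusion.** The conclusion in section 8.1 and the synopsis is stronger than the calculation behind it. A pass would show that any excess of Savi Scout failures over wire is below 0.9 points, which is non-inferiority. Two-sided equivalence at the same margin has about 55-67% power, depending on the interval method. At the assumed wire rate a pass excludes only a rate 2.5 times that of wire, and the study is not powered to exclude a 1.5-fold or 2-fold increase.

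These figures rest on 1000 patients in each group, although the wire cohort's size is not stated, and on the plan's 0.6% wire rate except where another is shown. The 1.5-fold pass probability moves in both directions with the wire rate: 76-84% at 0.3% and 19-22% at 1.0%. The sample size is adequate for the one-sided claim, and nothing here shows that it or the 0.9-point limit is wrong. The point is minor.

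**What to change.** Keep 1000 per group and the 0.9-point limit. In section 8.1 and the synopsis, replace the claim that the size is enough for equivalence with wording such as:

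> sufficient to exclude a Savi Scout failure rate more than 0.9 percentage points above wire (2.5 times the assumed wire rate of 0.6%); the study is not powered to exclude a 1.5-fold or 2-fold increase.

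Report the failure-rate ratio with an exact or score 95% confidence interval beside the difference. State what 0.9 points amounts to relative to the wire cohort's observed rate.

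Do not add a rule that bars the claim when the observed wire rate is below 0.6%. With 1000 wire patients and a true rate of exactly 0.6%, the chance of 5 or fewer failures is 44.5%, so the rule would apply almost half the time when the planning assumption is correct.

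The cost is a sentence in two places and one extra reported ratio, with no more patients. The downside is that the study's stated conclusion becomes weaker than equivalence.

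### The sample-size text claims equivalence from a one-sided upper-limit criterion that can support only non-inferiority

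*Protocol*

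**What the plan says.** Protocol section 8.1 sets the calculation out in two sentences, and the statistical considerations row of the synopsis repeats them.

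- **Size:** "with n=1000 patients per group".
- **Criterion:** it concerns "the upper limit of the observed one-sided 95% confidence interval for the difference between failure rates (seed vs wire"), which "is expected to be less than 0.9% with 80% power".
- **Planning rates:** "assuming the two methods both have an expected failure rate of 0.6" per cent.
- **Margin:** "if a 0.9% difference is considered an acceptable equivalence margin (eg. 0.6% for wire and 1.5% for seed").
- **Conclusion:** "1000 patients per group should be sufficient to establish equivalence".

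I take seed here to mean the Savi Scout reflector. Neither place gives a lower limit, a two-sided 90% interval or a pair of one-sided tests. Section 8.2 names summary statistics, regression and tests of difference, and adds no interval criterion. Section 3.2 lists the comparison with hookwire as a secondary objective.

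**The concern.** The criterion and the conclusion do not match. If the upper limit for seed minus wire is below 0.9 points, a seed failure rate higher than wire by 0.9 points or more has been ruled out. Nothing has been shown about the other direction. Equivalence also needs the lower limit to lie above -0.9 points.

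What is at stake is the claim that the study may make. This paragraph is the protocol's only sample-size justification, and the only place that says what 1000 patients per group will allow the authors to conclude. Authors who followed it literally could report equivalence from a one-sided limit, and readers could take the 80% as the power for that claim.

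**Working it through.** **Inputs, all from Protocol section 8.1:** n = 1000 per group; failure rate p = 0.006 in both groups, so the true difference is 0; margin m = 0.009; one-sided 95% limit, so z = 1.645.

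**1. The plan's own figure.**

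SE = sqrt(2 × 0.006 × 0.994 / 1000) = 0.00345, or 0.345 percentage points.

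- Limit met with 80% power: (1.645 + 0.842) × 0.345 = 0.859 points, which rounds to the stated 0.9.
- Power with 0.9 taken as exact: Φ(0.009/0.003454 − 1.645) = Φ(0.961) = 83.2%.
- n per group for 80% power: (1.645 + 0.842)² × 2 × 0.006 × 0.994 / 0.009² = 911 after rounding up.

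The stated sentence is therefore true by the usual approximation, with a little to spare. A one-sided 2.5% level does not fit as well: it gives 74.1% power and 1156 per group.

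**2. Check without the normal approximation.** Only 1000 × 0.006 = 6 failures are expected per group, so I also summed the binomial probabilities over all pairs of failure counts from 0 to 40 in each group. The upper limit falls below 0.9 points with probability 83.5% for Wald limits and 77.6% for Newcombe limits.

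**3. What the word equivalence would require.** Equivalence within ±0.9 points needs the upper limit below +0.9 and the lower limit above −0.9, each at one-sided 5%.

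- Power at 1000 per group: 2 × Φ(0.961) − 1 = 2 × 0.832 − 1 = 66.3%.
- n per group for 80% power: (1.645 + 1.282)² × 2 × 0.006 × 0.994 / 0.009² = 1262 after rounding up.

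| Claim at 1000 per group, one-sided 5% | Normal approximation | Enumeration, Wald | Enumeration, Newcombe | n per group for 80% (normal approximation) |
| --- | --- | --- | --- | --- |
| Upper limit below 0.9 points (non-inferiority) | 83.2% | 83.5% | 77.6% | 911 |
| Both limits within ±0.9 points (equivalence) | 66.3% | 67.0% | 55.2% | 1262 |

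The stated 1000 and 80% belong with the first row.

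**4. Does a lower bound of −0.9 points make sense here?** With wire at 0.6%, the lowest possible true difference is 0 − 0.6 = −0.6 points. A difference of −0.9 would need a seed failure rate of 0.6 − 0.9 = −0.3%, which cannot occur. Under the planning rates a symmetric margin has little meaning.

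**The case against.** The strongest reply is that this is a matter of terminology. The 80% is attached in so many words to the one-sided upper limit, where it holds by the usual approximation. The only example of the margin runs from 0.6% for wire to 1.5% for seed, so the direction of interest is plain, and a statistical reader would recognise non-inferiority. The comparison is a secondary objective of a non-randomised audit, and a statistical analysis plan that is not shown could set the interval and the wording.

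Most of this stands, and it limits the seriousness of the point. It does not remove it. The protocol states the wrong conclusion in two places, and nothing else in it corrects that. That the authors probably meant non-inferiority is a reason to say so.

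Three stronger readings are tempting:

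- **A reader might infer that the comparison has only 66% power, or that 1262 per group are needed.** Those figures describe a two-sided test that the protocol never specifies, with a lower bound that is impossible at the assumed wire rate. They show only how far apart the two claims are.
- **A reader might infer that the 80% was miscalculated.** It was not: the figure reproduces for the criterion to which the text attaches it. With Newcombe limits it falls slightly short, at 77.6%. If that interval is cited for equivalence (55.2%), it must be cited for non-inferiority as well.
- **A reader might infer that the report will claim equivalence.** That is a risk created by the wording. Section 8.2 sets out no equivalence test.

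**Conclusion.** The point holds as a mismatch between criterion and conclusion. The calculation in section 8.1 and the synopsis is a sound non-inferiority calculation, and the word equivalence is wrong for it. Power for the criterion as written is 83% by the normal approximation and about 78% by enumeration with Newcombe limits, so the stated 80% is fair. The same inputs would give about 66% and 55% for two-sided equivalence.

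These figures rest on the protocol's own assumptions: a true failure rate of 0.6% in both groups, 1000 patients in each, and independent observations. With about six expected failures per group they are sensitive to the interval method. The conclusion about the label is not, because an upper limit alone never establishes equivalence.

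This should be fixed, since it changes what the study may claim. It concerns a secondary comparison and calls for no change in design or size.

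**What to change.** In Protocol section 8.1 and in the statistical considerations row of the synopsis:

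- replace equivalence with non-inferiority, and equivalence margin with non-inferiority margin;
- limit the conclusion to this: the Savi Scout failure rate is not higher than that of wire by 0.9 percentage points or more;
- do not offer two-sided equivalence as an alternative, since a −0.9 point bound has little meaning at a 0.6% wire failure rate.

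The sample size stays at 1000 per group and data collection is unchanged. The cost is a few words in two places and a more modest claim.
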